#### Secondary outcomes

Secondary outcomes will comprise changes in the severity of self-reported anxiety and insomnia symptoms respectively. Anxiety symptoms will be assessed measured by the State Trait Personality Inventory (STPI – Trait only) [39]. The STPI is a self-administered questionnaire designed to measure dispositional anxiety, anger, depression and curiosity in adults i.e. how they “generally feel”. It consists of four 10-item subscales with each item rated on a four-point frequency scale. Higher scores are positively correlated with higher levels of dispositional emotional states. The STPI is a widely used measure and has high validity and reliability, particularly for the anxiety and anger scales [39]. Mean changes in total summed scores from baseline to three-month follow-up will be compared between the two randomised groups.

Insomnia symptoms will be measured by the Insomnia Severity Index (ISI) [27], which assesses insomnia symptom severity, distress and daytime impairment over the past two weeks. Each of the seven items are assessed on a likert-based scale which provide an overall quantitative score ranging from 0 to 28, with higher scores indicative of more severe insomnia. The tool has been shown to be a valid and reliable measure [27] and is sensitive to change following intervention for primary insomnia in older adults [40]. In the current investigation, mean changes in continuous insomnia symptom scores from baseline will be compared between the two randomised groups at three-month follow-up.

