### Objectives

In older men with major depression, this trial aims to:Investigate the efficacy of SHUTi as an adjunctive treatment to standard *beyondblue* guideline-based treatment [23,24] for reducing depression symptom severity;Determine whether adjunctive SHUTi decreases anxiety and insomnia symptom severity;Ascertain whether SHUTi is associated with changes in actigraphy/sleep diary determined sleep in people with comorbid depression and insomnia symptoms;Explore the processes, predictors and mediators of treatment response and of adherence to SHUTi by determining user characteristics and behaviours that may predict positive outcomes, adherence, trial drop-out, and program acceptability.

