### Clinical treatment for depression

As part of standard treatment for depression, all participants will undergo a clinical assessment with a psychiatrist prior to study commencement, whereupon a depression treatment plan will be prepared in accordance with clinical practice guidelines [23,24]. This will include watchful waiting, referral to psychotherapy or other interventions such as couple therapy, or medication use under standard collaborative care with the patient’s GP. The assessment will include the Mood Episode and Disorder modules, and the Substance Abuse screens of the SCID, standard clinician rated measures: the 17-item Hamilton Rating Scale for Depression (HAM-D) [32], and the Hamilton Rating Scale for Anxiety (HAM-A) [33], Mini Mental State Examination [28], Global Assessment of Functioning (GAF) [34], Social and Occupational Functioning Assessment Scale (SOFAS) [35] and Cumulative Illness Rating Scale for Geriatrics (CIRS-G) [36] as well as completion of a full psychiatric and medical history. After two weeks, participants will be required to undergo a clinical review with the psychiatrist, in accordance with their treatment plan. Over the subsequent nine weeks, participants will undergo further psychiatric review and management as clinically required. Standard clinical instruments will be administered to monitor depressive symptoms over this period. If any changes to medication dosage are required, this will be discussed between the patient, trial psychiatrist and/or referring doctor. At the end of the trial period the participant will be referred back to their GP or treating doctor, or if required, managed in the trial clinic until appropriate for discharge.

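### The score for the secondary anxiety outcome is the summed STPI total; read literally, this mixes four constructs and cannot isolate anxiety, so the 10-item anxiety subscale should be named

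*Protocol article*

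**What the plan says.** The second aim under Objectives is "Determine whether adjunctive SHUTi decreases anxiety and insomnia symptom severity". Secondary outcomes turns this into an endpoint: "Secondary outcomes will comprise changes in the severity of self-reported anxiety and insomnia symptoms respectively". For anxiety, the instrument is the STPI, trait form only.

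The same section describes that instrument as "designed to measure dispositional anxiety, anger, depression and curiosity in adults", based on how people generally feel. On its structure: "It consists of four 10-item subscales with each item rated on a four-point frequency scale". On its direction: "Higher scores are positively correlated with higher levels of dispositional emotional states". The score to be analysed is then given as: "Mean changes in total summed scores from baseline to three-month follow-up will be compared between the two randomised groups".

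Table 1 lists the STPI as an anxiety measure at baseline, Week 12 and Week 36, without naming a subscale. The Hamilton Rating Scale for Anxiety (HAM-A) appears in Table 1 at baseline and Week 12. It enters the analysis under Tertiary outcomes, as one of the clinician-rated scales.

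**The concern.** The outcome is anxiety, but the stated score is the total of an instrument that the article itself describes as covering four constructs. An analyst who follows the sentence as written would sum all 40 items.

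That has three consequences:
- A quarter of the score would carry the construct of interest.
- The depression subscale measures much the same thing as the primary outcome, so an effect on mood alone could appear as an effect on anxiety.
- Curiosity is scored in the same upward direction as the distress subscales, with no reversal stated, so a rise in curiosity would offset a fall in anxiety.

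At stake is what a result on this endpoint means. A positive difference could not be attributed to anxiety, and a null one could hide an anxiety effect. If the intended score is left unsettled, the choice between the total and the subscale also stays open until data are seen.

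**Working it through.** **What is summed.** From Secondary outcomes: 4 subscales × 10 items = 40 items. Anxiety items: 10/40 = 25%. The other 30 items are anger, depression and curiosity.

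**The plan's own figure.** Sample size gives 40 per group, or 36 per group with 10% attrition: 36/(1 − 0.10) = 40, which reproduces. The plan states no effect size or power for anxiety, so there is no anxiety figure to reproduce. The rest is illustration.

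**Assumptions, none from the documents.** The four subscales have equal SDs (set to 1). The correlation is r = 0.3 to 0.7 among anxiety, anger and depression, and c = 0 to −0.3 between each of these and curiosity. The effect on the anxiety subscale is 0.40 SD.

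**SD of the total.** Variance = 4 + 2(3r + 3c) = 4 + 6r + 6c. The effect on the total is the net sum of the subscale changes divided by the SD. The four corners of the assumed range are:

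| r | c | Variance | SD | Only anxiety improves 0.40 | Anxiety and depression improve 0.40, curiosity rises 0.20 | Anxiety, anger and depression improve 0.40 | The same three improve 0.40, curiosity rises 0.20 |
|---|---|---|---|---|---|---|---|
| 0.3 | 0 | 5.8 | 2.408 | 0.17 | 0.25 | 0.50 | 0.42 |
| 0.3 | −0.3 | 4.0 | 2.000 | 0.20 | 0.30 | 0.60 | 0.50 |
| 0.7 | 0 | 8.2 | 2.864 | 0.14 | 0.21 | 0.42 | 0.35 |
| 0.7 | −0.3 | 6.4 | 2.530 | 0.16 | 0.24 | 0.47 | 0.40 |

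The numerators of the last four columns are 0.40, 0.40 + 0.40 − 0.20 = 0.60, 3 × 0.40 = 1.20, and 1.20 − 0.20 = 1.00.

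**Specificity.** If anxiety does not change and only depression improves by 0.40 SD, the numerator is again 0.40. The total then shows the same 0.14 to 0.20 SD. From the total alone, the two cases cannot be told apart.

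**Power, for scale only.** With 36 per group and an assumed two-sided 5% test, power ≈ Φ(d√(36/2) − 1.96) = Φ(4.243d − 1.96).
- Anxiety subscale, d = 0.40: Φ(−0.263) = 0.40.
- Total when only anxiety moves, d = 0.14 to 0.20: 0.09 to 0.13.

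**The case against.** The best defence is that the sentence was never meant to combine subscales. The outcome is named as anxiety, Table 1 labels the STPI an anxiety measure, and the article cites validity and reliability for the anxiety and anger scales in particular, treating them as distinct. It also uses the word summed for ordinary single-scale totals: the CES-D and HAM-D under Primary outcome, and the HAM-D under Sequence generation. An anxiety-subscale sum is therefore a plausible intention, and a full protocol or SAP may say so. This stands as an account of intent. It does not remove the point, because the article does more than stay silent on scoring: it states a score, and that score does not match the named outcome.

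It is also fair to object that dilution is not assured. The low figures assume that anger does not move. If anger and depression improve as much as anxiety and curiosity is unchanged, the total shows 0.42 to 0.60 SD, no smaller than the anxiety effect. This stands too. It limits the claim about size, but not the claim that the total is not specific to anxiety.

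A reader might go further in three ways that the documents do not support.
- **That the trial cannot answer its anxiety objective.** The HAM-A is measured at baseline and Week 12 and is planned as a tertiary outcome, so anxiety is assessed apart from the STPI total.
- **That the trait form is an error.** There is some tension between how people generally feel and change in symptom severity over about three months. But the article states the choice openly, and nothing in it shows that the scale cannot change over that time.
- **That the HAM-A should replace the STPI as the secondary outcome.** The secondary outcome is declared as self-reported and the HAM-A is clinician-rated, so the swap would change what is estimated. Table 1 also has no HAM-A at Week 36. This is a matter of preference, not a correction.

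**Conclusion.** The point holds as a mismatch between a stated score and the outcome it is meant to measure. As written, the STPI total contains 10 anxiety items out of 40, shares content with the primary depression outcome, and includes a subscale with no stated reversal. It cannot separate an effect on anxiety from effects on the other constructs. That conclusion rests only on the article's own description of the instrument.

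The size and direction of any distortion are not established. Under the assumed equal SDs and correlations, a 0.40 SD effect confined to anxiety appears as about 0.14 to 0.20 SD. With parallel improvement in anger and depression and no change in curiosity, there is no dilution. Whether the total was really intended is also open. The primary CES-D comparison is unaffected.

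**What to change.** In Secondary outcomes, replace the reference to total summed STPI scores with *the summed score of the 10-item trait-anxiety subscale*. The other subscales should not contribute to this endpoint. Table 1 could carry the same label.

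Keep the HAM-A change at Week 12 where it is, as a tertiary, clinician-rated measure, and read it alongside the subscale as supportive evidence on anxiety symptom severity.

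The cost is one phrase. The subscale items are already part of the STPI collected at baseline, Week 12 and Week 36, and neither the sample size nor the assessment schedule changes. If a full protocol or SAP already names the subscale, only the article's wording needs to be brought into line. The wording should be settled before outcome data are examined by arm.

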#### Tertiary outcomes

Changes in actigraphic and sleep diary assessed sleep parameters (total sleep time, sleep efficiency, wake after sleep onset, sleep onset latency), hypnotic use, sleep beliefs (Dysfunctional Beliefs about Sleep (DBAS); [41]), the clinician rated scales above and self reported health related quality of life (Medical Outcomes Study Short-Form Health Survey; SF-12) will be measured at baseline and post-intervention. In addition, user characteristics predictive of outcome such as demographic, health and lifestyle factors will be described by treatment group at trial entry and overall at three and six months. Program adherence and drop-out will be monitored throughout the intervention period, and evaluation measures will be measured at post-intervention.

### Participant timeline

Potential participants will visit the trial-specific website www.somna.com.au where they will be provided with detailed information about the trial, the procedures and time commitment involved in participation, the randomisation process, and confidentiality, and contact details for the trial team should they want further information. The Participant Information Statement and Consent Form will be published on the website and available for download. Those interested in participating in the trial will undertake an online consent and preliminary eligibility screening procedure.

Completion of online consent and preliminary eligibility screening requires potential participants to provide their full name and contact details, along with their date of birth, gender and confirmation of their regular access to an internet-enabled computer or device and availability to attend the Trial Coordinating Centre on at least four occasions. Potential participants will then be asked general information pertaining to current sleep habits, and to complete the QIDS-SR, ISI and RLS screening tools. Interested participants are asked to sign the consent form by dragging their mouse to create their signature, thus giving permission to the research team to assess their preliminary screening responses and contact them to conduct an interview over the telephone to further confirm eligibility to participate. This process also creates a unique profile (trial identification number) for the potential participant within the trial website.

Upon submission of the online consent and preliminary screening questionnaire, a member of the SOMNA trial team will assess the potential participant’s eligibility against the trial inclusion criteria. Those that do not meet criteria will receive an email outlining why they have not been selected to participate and will be provided with a resource sheet outlining options for alternative treatment or support for depression and sleep concerns. A research assistant will contact those who meet trial inclusion criteria via telephone, and an interview assessment against the trial exclusion criteria will be completed. Participants who do not meet criteria, due to prior diagnosis of psychosis or hypo/manic episodes, high risk or prior diagnosis of sleep apnea, or who report they are a rotating shift worker, will be thanked for their time and will not participate further. If required further referral information will be provided. If potential participants report recent transmeridian travel, they will be invited to undergo all preliminary depression and insomnia screening questions again once they have had opportunity to readjust to the present time zone. Wherever psychiatric history is unclear, participants will be invited to attend for baseline assessment whereby the trial psychiatrist will undertake a comprehensive clinical interview to confirm diagnosis.

Following telephone screening, all eligible participants will be invited to attend the Trial Coordinating Centre (Brain & Mind Research Institute, Sydney, Australia) to commence baseline assessment. Whilst at the Trial Coordinating Centre, the participant will complete the baseline medical assessment and clinical interview and an online self-report questionnaire. Ongoing participation in the trial will be measured from this time-point. As part of the baseline assessment, participants will be provided with an actigraphy watch to wear on their wrist for the subsequent two weeks, and they will be instructed to log into the SOMNA website each day during this period to submit sleep diaries. Upon completion of ten diaries in a 14-night period the participant will be eligible to commence the active/control intervention. Full informed, written, consent will be obtained prior to any study procedure being undertaken.

Upon completion of the nine-week intervention period, participants will be prompted by automated email to return to the trial website to complete the post-intervention self-report questionnaire. Personalised emails, text message reminders and telephone calls will be made to participants who do not respond to encourage completion. Participants will also be invited to return to the Trial Coordinating Centre to complete the post-intervention medical assessment, and have the option of completing the online questionnaire at that time too. As per the baseline assessment, they will be provided with an actigraphy watch to wear on their wrist for the subsequent two weeks, and they will be instructed to log into the SOMNA website each day during this period to submit sleep diaries.

A final follow-up assessment will be completed six-months later, although on this occasion only self-report measures will be collected through the study website. Personalised emails, text message reminders and telephone calls will be made to participants who do not initially respond. Refer to Figure 1 for further detail regarding the timeframe for follow-up assessments.

Where participants are unable to complete follow-up self-report assessments online, a hardcopy of the assessment will be mailed to them for completion at home. Alternatively, a blinded research assistant may complete the assessment over the telephone. Where a participant discontinues their assigned intervention, all efforts will be made to retain the participant in the trial to enable follow-up data collection and prevent missing data.

### Sample size

In older adults, literature suggests depression treatment comprising pharmacotherapy or psychotherapy will elicit medium effects on symptomology. In the secondary analysis of the primary SHUTi trial, the effect of the intervention on depressive symptoms was larger than this, with a reported effect size on reducing depressive symptoms of 0.72 pre and post assessment using the Beck Depression Inventory [22]. Although noting this was detected amongst a community sample with mild depressive symptoms, we hypothesise that an adjunctive SHUTi intervention will lead to a small to moderate effect size over and above the effect of standard guideline-based depression treatment in a naturalistic setting. We propose to conduct a randomised controlled trial that will seek to establish the true effect size, along with feasibility of conducting a definitive clinical trial in a large-scale primary care setting that would provide evidence on the potential benefit of an adjunctive insomnia intervention for depression amongst older men. We will attempt to recruit a minimum of 80 participants with 40 per group (36 per group with 10% attrition) for the comparison of endpoint depression scores between the SHUTi intervention and the control condition.

### Recruitment

Trial participants will be recruited into the study on a rolling basis over a period of 18-months. The entire study is expected to be complete within three years.

### Allocation

The allocation of participants to study arm will be undertaken by a staff member who is independent of the study operations and has no day-to-day contact with participants. Once full informed consent is obtained and the trial psychiatrist has assessed eligibility and made the decision to enrol a participant, a research assistant will notify the independent staff member to perform the random allocation. Treatment allocation will be undertaken in accordance with the electronic randomisation schedule, which will be generated by the unblinded trial manager prior to trial commencement, password-protected and saved on a secure network. In addition to documenting each allocation on the randomisation schedule, so as to generate a unique username and password to enable each randomised participant access to their allocated website program, the independent staff member will be required to assign the allocated program to the user’s profile in the trial website.

### Sequence generation

The allocation sequence will be generated using a randomly generated number sequence calculated used Research Randomizer (http://www.randomizer.org/) prior to trial commencement. The fully replicable sequence will be based on permuted blocks, and eligible participants will be stratified according to presenting depression severity (their summed HAM-D score obtained during the baseline medical assessment and clinical review) to ensure participants with higher levels of symptoms are distributed equally across both conditions. In accordance with severity classification that maximises the sensitivity and specificity of the HAM-D scale, symptom severity will be collapsed into two categories including *mild-moderate* scores <17; *moderate-severe* scores ≥17 [42]. The allocation sequences within each strata will be pre-generated by the unblinded trial manager and documented in the randomisation schedule prior to trial commencement.

### Allocation concealment mechanism

The allocation codes will be saved in a password-protected file accessible only to the independent staff member who performs randomisation and the unblinded trial manager, not to be provided until the completion of the trial, unless unblinding is required in an emergency. The allocation code assigned to any participant will only be broken by the Chief Investigator or trial manager if the patient’s safety is at risk and it is absolutely necessary to ascertain the website program they were allocated. Given the low risk of the intervention under study, this scenario is unlikely to eventuate. However, where patient safety is under consideration, disabling access to the website program will be the preferred management option in contrast to unblinding.

### Blinding (masking)

This is a double-blind clinical trial whereby the study participants and the clinical investigators / trial monitoring staff, including the treating psychiatrist, will be unaware of treatment assignment. Only the trial manager, the Internet program system administrator and the trial statistician will have access to unblinded data at the individual level. However, they will not have any direct access to trial participants.

Several strategies will be employed to minimise bias through accidental unblinding. Knowledge of treatment allocation will be minimised by virtue of the intervention delivery method being web-based, along with all self-report assessments. Personnel who are unaware of the participant’s treatment allocation will assess all clinical outcomes. On each occasion of clinical assessment, participants will be reminded that staff must remain blinded to treatment allocation, and as such they should refrain from describing or discussing their website program. In the event that treatment allocation is accidentally revealed to a staff member during an assessment, an alternative assessor, who is blind to allocation, will conduct subsequent follow-up assessments. The trial manager will maintain an unblinding log to record any specific personnel that may be accidentally (or deliberately) unblinded during the course of the trial, along with the date, scope and reason for doing so.

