**Assessments**								
Informed consent	**X**	**X**						
Inclusion/exclusion criteria	**X**	**X**						
Self report measures		**X**		**X**	**X**		**X**	
Sleep diary		**X**			**X**		**X**	
Actigraphy		**X**			**X**			
Psychiatric assessment		**X**			**X**			**X**
Medical check-up*		**X**	**X**		**X**			
Monitor for suicidality*		**X**	**X**		**X**			**X**
Adverse events*			**X**		**X**			**X**

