### Safety and event monitoring

The intervention under study is considered low-risk, with the only safety concern associated with the active SHUTi intervention related to increased tiredness and its sequelae due to restricted time spent in bed (as per the behavioural treatment for insomnia). This risk is mitigated directly through the program, which does not restrict sleep by fewer than five hours. In light of this, and given that all trial participants will be under the clinical care of their treating psychiatrist throughout the intervention period, an independent Data and Safety Monitoring Committee will not be established.

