### Harms

During the course of the study, participants will be assessed for both expected and unexpected adverse events (AEs) at each clinical and research assessment time point. Adverse events will be defined as any unfavourable and unintended sign, symptom or disease temporarily associated with the use of the intervention under investigation. Medical conditions or diseases present before starting the intervention will be considered adverse events only if they worsen after starting the trial and that worsening is considered to be related to the study intervention. An AE will also be extended to include any undesirable and unintended effect of research occurring in trial participants as a result of the collection of identifiable private information under the research. An AE will be deemed serious if it is determined to be associated, or possibly associated with study involvement, and results in either: death, is life-threatening, requires or prolongs hospitalisation, or results in persistent or significant disability or incapacity. Expected AEs will include: initial discomfort or embarrassment due to personal or sensitive nature of research questions; concerns related to internet-based data collection and storage procedures; and initial tiredness, fatigue and possible concentration problems as a result of sleep restriction techniques to improve sleep habits.

Adverse events will be detected at the Week 3 clinical review and Week 12 follow-up assessment. In addition, research assistants conducting routine monitoring telephone interviews at Weeks 4 and 8, will also have capacity to detect AEs.

All AEs (including Serious Adverse Events, or SAEs), regardless of relatedness to the interventions under investigation, will be recorded, classified and graded on an adverse event form. Recording will be completed in a concise manner using standard, acceptable medical terms. All SAEs will be reported to the Human Research Ethics Committee within 72 hours.

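### The reminder not to discuss the website program has no stated exception for harms, so sleep-restriction tiredness may be under-attributed or under-reported, mainly in the SHUTi arm

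*Protocol article*

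**What the plan says.** **The blinding rule.** The section Blinding (masking) states: "On each occasion of clinical assessment, participants will be reminded that staff must remain blinded to treatment allocation". The request then made of the men is that "they should refrain from describing or discussing their website program". If allocation is revealed, another blinded assessor takes over later assessments. Clinical and monitoring staff, "including the treating psychiatrist, will be unaware of treatment assignment".

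**The harm.** Safety and event monitoring describes "the only safety concern associated with the active SHUTi intervention related to increased tiredness and its sequelae due to restricted time spent in bed". Harms lists among the expected events "initial tiredness, fatigue and possible concentration problems as a result of sleep restriction techniques to improve sleep habits".

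**Collection.** Harms says "Adverse events will be detected at the Week 3 clinical review and Week 12 follow-up assessment", and adds that "research assistants conducting routine monitoring telephone interviews at Weeks 4 and 8, will also have capacity to detect AEs". In Table 1 the row "Adverse events" is marked at Visit 1 (Week 3), Week 12 and early termination. As far as the extracted table can be read, the cell for the Week 4 and 8 calls is empty. A footnote allows further clinical reviews according to each man's treatment plan.

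**Relatedness.** Harms records all adverse events whatever their relatedness. It also counts a condition present before the intervention as an adverse event only if it worsens and the worsening is judged related. An event is serious only if it is associated, or possibly associated, with taking part.

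**The concern.** The blinding rule and the safety rule meet at the same visits and pull in different directions. A man who wants to explain that his tiredness began when the program shortened his time in bed has just been asked not to talk about the program. Nothing in the article tells him that problems are exempt.

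The reminder is worded alike for both arms but does not weigh on them alike. Tailored sleep restriction is a SHUTi component, while the control program is basic text needing about 30 minutes. If explanations or reports are lost, the loss would fall mainly on the active arm. The safety analysis announced under Statistical methods would then lean towards no harm, in a trial meant to inform a definitive one.

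**Working it through.** **Step 1. Where the reminder and adverse-event collection coincide.** Trial design places two weeks of baseline measurement before the program, so the nine weeks run from about Week 3 to Week 12 (3 + 9 = 12).

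| Contact | Reminder given? | Adverse events collected? | Time on program |
|---|---|---|---|
| Week 3 review | Yes | Yes (Harms, Table 1) | About 0 weeks |
| Calls, Weeks 4 and 8 | Not clear; the article does not say whether they count as clinical assessments | Harms: capacity to detect; Table 1: not marked | About 1 and 5 weeks (4 − 3, 8 − 3) |
| Week 12 assessment | Yes | Yes (Harms, Table 1) | Full nine weeks |
| Early termination | Yes, if its psychiatric assessment is a clinical assessment | Yes (Table 1) | Varies |
| Extra individual reviews | Yes, if clinical assessments | Allowed by the Table 1 footnote | Varies; number not fixed |

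Week 3 carries little weight, because sleep restriction has hardly begun. The fixed overlap that matters is Week 12, plus early termination. Week 12 is also late for a harm that the article calls initial.

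**Step 2. Does recording everything whatever its relatedness settle the matter?** Not fully. Eligibility requires a current depressive disorder and insomnia symptoms above threshold. Tiredness and poor concentration can readily be read as part of those conditions. For a man who already had them, worsening becomes an adverse event only after a judgement of relatedness. That judgement is better informed if he can say what the program asked of him, which is what the reminder discourages. The gate applies in both arms, but events actually caused by tailored sleep restriction would be lost mainly from the SHUTi arm.

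**Step 3. Size.** The article gives no rate of tiredness and no reporting fraction, so there is no figure of its own to reproduce here. The only usable input is the planned 40 per group, which is consistent with 36 after 10% attrition (36 / 0.9 = 40). What follows is illustration on assumed rates, not evidence that any loss occurs.

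Recorded difference = rT × pT − rC × pC, where p is the true proportion with tiredness and r the fraction recorded. Assume pT = 20% and pC = 5%:

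| rT | rC | SHUTi, of 40 | Control, of 40 | Recorded difference |
|---|---|---|---|---|
| 1 | 1 | 8 | 2 | 15 points |
| 0.75 | 1 | 6 | 2 | 10 points |
| 0.5 | 1 | 4 | 2 | 5 points |
| 0.5 | 0.5 | 4 | 1 | 7.5 points |

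The last row shows equal loss: the ratio stays at 4 (8/2 and 4/1), although the absolute difference still shrinks.

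For a two-sided 5% comparison of two proportions with 40 per arm (the article gives 5% without saying one- or two-sided), power is Φ[(d − 1.96 × se0) / se1], with se0 from the pooled and se1 from the separate proportions. With assumed true rates of 30% and 10%: d = 0.20, se0 = √(2 × 0.2 × 0.8 / 40) = 0.0894, se1 = √((0.21 + 0.09) / 40) = 0.0866, giving 61%. If only SHUTi reports are lost, power falls to 33% at 75% reporting and 10% at 50%. With 40% and 10% the three values are 89%, 61% and 24%.

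**The case against.** A reader might infer that the harm is in fact under-reported and that blinded staff cannot judge relatedness. The documents support neither.

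- The reminder concerns the program, not symptoms. A man can say that he is exhausted without mentioning a website.
- Tiredness, fatigue and concentration problems are listed in advance as expected events. Harms also says that participants are assessed for expected and unexpected events at every clinical and research time point.
- Judging causality while blinded is normal in a double-blind trial. The test for seriousness asks only about possible association with taking part, which does not need the arm, and the code can be broken for safety.
- The Week 4 and 8 calls are a further route, and the reminder is not clearly given there. The ISI, which includes daytime impairment, is collected in both arms at Weeks 4, 8 and 12.
- The control program also mentions behavioural and cognitive techniques, so control men too have content that they are asked not to discuss.
- An article may leave the reminder script and the adverse-event questions to the full protocol.

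Most of this stands and limits the point to a possible loss of unknown size. Three things remain. The article gives the content of the reminder without an exception for harms. The relatedness gate for pre-existing conditions is stated, and it bears on symptoms that this population may well bring to the trial. And the two accounts of the calls differ, with Harms giving them a detecting role and Table 1 marking none. The ISI does not fill the gap: it is an outcome scale, and its total can fall as sleep improves even if daytime tiredness rises.

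**Conclusion.** The concern holds as a possible bias, not a demonstrated one. The reminder coincides with the fixed face-to-face collection of adverse events after real exposure, essentially at Week 12 and early termination. Together with the relatedness gate, it may lead to under-attribution or under-reporting of the only safety concern named for SHUTi. If so, a safety comparison by randomised arm would lean towards no harm.

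This rests on two assumptions: that some men take the reminder to cover program-related problems, and that some staff read worsened tiredness or concentration as part of the existing illness. The documents show neither, and they give no rate from which a size could be computed. The point deserves a clarification because that is cheap, not because harm data are known to be lost.

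**What to change.** 1. Add to the reminder in Blinding (masking) that it never covers symptoms or problems, which should always be reported.
2. Ask the same fixed, allocation-neutral questions in both arms about the expected harms listed under Harms (tiredness, fatigue, concentration problems), at the Week 4 and 8 calls and in the Week 12 online form. Nobody then needs to mention the program.
3. Mark adverse-event collection at the calls in Table 1, so that it agrees with Harms.
4. Record any new or worsened symptom whatever its relatedness, including worsening of a pre-existing condition, and reconcile the definition in Harms with this. The comparison by randomised arm then does not depend on individual attribution.

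Having the unblinded trial manager classify relatedness is not a good alternative. It would bring expectation bias into the classification, and step 4 makes it unnecessary for the comparison.

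The cost is a sentence in the reminder, slightly longer forms and calls, and a small risk that an answer about symptoms hints at the arm. The online form limits that risk at Week 12.
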